### Statistical analysis

#### Study parameter(s) indicator study

Non-continuous data will be reported as frequencies. Continuous variables normally distributed will be reported as mean ± standard deviation (SD). Not normally distributed data will be reported as median (interquartile range, IQR). The analytical plan consists of two steps. The first step will be to explore the discriminating power of meeting two or more criteria of the set of indicators for predicting death within one year and predicting unexpected hospital admission, respectively. The sensitivity and specificity for both death within one year and for unexpected admission to hospital will be presented. The second step will be to explore the discriminating power of individual indicators (or clusters) in predicting death within one year or unexpected admission to hospital. Univariable and multivariable logistic regression will be performed to examine which variables or cluster of variables are associated with death within one year (unexpected admission to hospital respectively). Variables will be eliminated one by one from the model based on likelihood ratio tests. Variables are eligible for inclusion into the final model if they are significantly associated with death within one year (unexpected admission to hospital respectively), with a p-value of < 0.10.

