Unfortunately, no research data is available on the beneficial effects of a multidisciplinary approach to proactive palliative care for patients with COPD in terms of reducing the healthcare utilization (for example, hospital readmission) or improving quality of life. However, in a study in male patients predominantly diagnosed with cancer but also with cardiovascular and pulmonary diseases, the benefits of palliative care provision appeared effective compared with usual care [33]. Patients receiving palliative care were less likely to be admitted to the ICU during hospitalization, had lower inpatient cost per day and received better medical care provision compared to usual care patients. Hence proactive palliative care may avoid admission to the ICU for patients with COPD and may help to reduce health care costs. More research data is available concerning the beneficial effects of an early introduction of palliative care for patients with cancer. In a recent study [34] the effect of introducing early palliative care among patients diagnosed with metastatic non-small-cell lung cancer was examined in a randomized controlled trial (RCT). As compared to patients receiving standard care, patients receiving early palliative care had a better quality of life, less depressive symptoms, less aggressive care at the end of life and longer survival.

In the present study the effects of proactive palliative care performed by a specialized palliative care team for patients with COPD on the wellbeing of these patients and their informal caregivers will be examined. We hypothesize that proactive palliative care for patients with COPD will: increase the quality of life of these patients, decrease the number and length of acute hospital admissions and ICU admissions, prolong survival of these patients, decrease the number of patients that die in the ICU, and decrease the level of overburdening of their informal caregivers.

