#### Controlled trial (assessment)

##### Patient

Patients in the control condition will receive standard care (usual care) only. Patients in the intervention condition will receive standard care and, only if they meet two or more criteria of the set of indicators for proactive palliative care they will receive proactive palliative care integrated with standard care. The procedure in the control condition will be first described before describing the procedure in the intervention condition.

In the hospitals in the control condition eligible patients will be recruited the second day after hospital admission. The treating lung specialist will give each eligible patient oral and written information about the study. The written information consists of an information leaflet and two informed consent forms: one for the patient and one for the informal caregiver. In the information leaflet a description of the study, including the nature of participation and phone numbers for study contacts, are given for the patient and the informal caregiver. The lung specialist will obtain written informed consent from the patient prior to enrollment. If a patient has consented, a lung nurse will distribute questionnaires for completion on the sixth day of hospital stay or in case the patient is discharged earlier on the day before leaving the clinic. After hospital discharge the patient will be asked by the study coordinator to complete questionnaires every 3 month until the end of the study or until death. The questionnaires will be sent to the patient by mail. A stamped retour envelope will be enclosed.

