##### Lung specialist

The treating lung specialist will provide standard care (usual care) to the patients hospitalized for an AECOPD. After the patient has filled out and returned the questionnaires the lung specialist in the control- and the intervention condition will fill out a case report form (CRF). The CRF consists of questions about the measurement results of each indicator of the set of indicators. The set of indicators is represented in Table 1. Only in the intervention condition the lung specialist will check if a patient meets two or more criteria of the set of indicators for proactive palliative care.

**Table 1 T1:** Set of indicators for proactive palliative care

**A patient hospitalized for AECOPD is eligible for proactive palliative care when meeting two or more criteria of the following set of indicators:**	
1.	Hypoxaemia or hypercapnia at discharge
2.	Treatment of the exacerbation with Non Invasive Ventilation (NIV)
3.	Patient needs professional home care service for personal care after discharge
4.	Negative answer to the surprise question: ‘Would I (as lung specialist) be surprised if this patient would have a subsequent readmission for AECOPD within 8 weeks and/or would die in the next year?
5.	The diagnosis of a severe comorbidity such as:
	a. Non-curable malignity or
	b. Cor pulmonale (proven or non proven) or
	c. Proven Chronic Heart Failure (CHF) or
	d. Diabetes mellitus with neuropathy or
	e. Renal failure, clearance < 40 (GFR: in ml/min)
6.	CCQ total, day version ≥ 3
7.	MRC dyspnea = 5
8.	FEV1 (measured before AECOPD) < 30% of predicted
9.	BMI < 21 or unplanned weight loss (> 10% weight loss in last 6 months or > 5% in last month)
10.	Previous hospital admissions for AECOPD (last 2 years ≥ 2 and/or last year ≥ 1)
11.	Age > 70 years

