#### Post-test assessment

A post-test assessment will be performed in all participating hospitals. The medical files of all participating patients will be examined retrospectively regarding the assessment period on the following measures:

● Number and length of hospitalization of unexpected hospital admissions for AECOPD

● Number and length of hospitalization of unexpected ICU admissions for AECOPD

● Are the choices of Advance Care Planning (ACP) documented in the medical file? (when yes/when no)

● Place of death (ICU/hospital/hospice/nursing/home/at home)

● Is preferred place of death known? (when yes/when no)

● Has this wish come true? (when yes/when no)

● Length of survival after meeting conditions for proactive palliative care

● The primary and secondary measures of the indicator study

In order to take account of possible confounding variables, other parameters are: age, gender, marital status, type of admission, (acute or planned), condition of living (single, or living together), place of living (home, residential home, or nursing home), Gold stage, comorbidities, and date of diagnosis.

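### The indicator analysis does not separate study conditions, although in intervention hospitals a positive indicator set triggers care hypothesised to reduce the predicted events; if that care works, discrimination is understated

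*Protocol article*

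**What the plan says.** - **Analysis.** Under Statistical analysis, Study parameter(s) indicator study, the first step is to "explore the discriminating power of meeting two or more criteria of the set of indicators for predicting death within one year", and likewise for unexpected admission, reported as sensitivity and specificity. For the second step, "Univariable and multivariable logistic regression will be performed to examine which variables or cluster of variables are associated with death within one year". Variables are removed by likelihood ratio tests, with a p-value below 0.10 required for the final model. Study condition appears in neither step.
- **Who contributes data.** The section Lung specialist has indicator results recorded on a case report form in both conditions. Under Post-test assessment, "A post-test assessment will be performed in all participating hospitals" and "The medical files of all participating patients will be examined retrospectively regarding the assessment period". The list of items there includes "The primary and secondary measures of the indicator study".
- **What a positive set triggers.** In the intervention condition, "only if they meet two or more criteria of the set of indicators for proactive palliative care they will receive proactive palliative care" (Controlled trial (assessment), Patient). The first meeting takes place before discharge if possible and otherwise within a week of enrolment, followed by monthly meetings for at least a year or until death. In control hospitals a positive set changes nothing.
- **What that care should do.** The protocol hypothesises that it will "decrease the number and length of acute hospital admissions and ICU admissions, prolong survival of these patients" (Organization of proactive palliative care for patients with COPD).
- **What the set should predict.** Readmission within 8 weeks and/or death within 1 year (Identification of patients with COPD for proactive palliative care).

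**The concern.** In half of the hospitals the test result decides who gets a treatment, and that treatment is expected to prevent the outcome against which the test is judged. It starts inside both prediction windows. A positive patient who would have died under usual care but survives because of the care is counted as a false positive. The two parts of the study then pull against each other: the better the care works, the weaker the indicators look.

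At stake is the primary objective of the indicator study. A pooled figure describes a mixture of usual care and indicator-triggered care that exists in no single hospital. A clinician deciding whether the set identifies patients with a poor prognosis needs the usual-care figure. Attenuated associations could also cause a useful indicator to be eliminated in the regression step. A larger sample would not remove the shift.

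**Working it through.** The protocol states no accuracy target or sample size for the indicator study, so there is no figure of its own to reproduce.

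**1. Share of patients affected.** Sample size calculation gives 29 indicator-positive patients per hospital out of 60 to 90 included. Study design puts 3 of 6 hospitals in the intervention condition.
- Positive share: 29/90 = 32% to 29/60 = 48%.
- Positive and in an intervention hospital: 0.5 × 32% = 16% to 0.5 × 48% = 24%.

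**2. Size of the shift (assumed inputs).** The document gives no mortality by indicator status and no expected effect on survival. Assume 40% positive (inside the 32–48% range), one-year mortality under usual care of 30% in positives and 10% in negatives, half of the positives treated, and a mortality hazard ratio HR for the care.
- Risk in treated positives = 1 − 0.7^HR.
- Pooled risk in positives, r = (0.30 + treated risk)/2.
- Odds ratio = [r/(1 − r)] / (0.1/0.9).
- Sensitivity = 0.4r / (0.4r + 0.6 × 0.1).
- Specificity = 0.54 / [0.54 + 0.4(1 − r)], where 0.54 = 0.6 × 0.9.

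| Setting | Risk in positives | Odds ratio | Sensitivity | Specificity |
|---|---|---|---|---|
| Control hospitals | 0.300 | 3.86 | 0.667 | 0.659 |
| Pooled, HR 0.7 | 0.260 | 3.17 | 0.635 | 0.646 |
| Intervention hospitals, HR 0.7 | 0.221 | 2.55 | 0.596 | 0.634 |
| Pooled, HR 0.5 | 0.232 | 2.71 | 0.607 | 0.637 |
| Intervention hospitals, HR 0.5 | 0.163 | 1.76 | 0.521 | 0.617 |

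**3. Other assumptions.** The calculation was repeated with 29 positive of 60 or of 90, mortality of 30–40% in positives and 5–15% in negatives, and a relative risk of death with the care of 0.8 to 0.5. Compared with control hospitals alone, pooling lowers:
- the odds ratio by about 14% (2.43 to 2.10) to 36% (12.67 to 8.14);
- sensitivity by about 0.01 (0.882 to 0.871) to 0.07 (0.487 to 0.416);
- specificity by about 0.01 to 0.04.

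At a relative risk of 1, pooled and control-only results are identical.

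**4. Bias against precision.** Six hospitals with 60 to 90 patients each give 360 to 540 in all. With the step 2 assumptions and 360 patients:
- Pooled, HR 0.7: deaths = 360 × (0.4 × 0.260 + 0.06) ≈ 59; standard error of sensitivity = √(0.635 × 0.365/59) ≈ 6.3 points; bias 3.2 points; root mean squared error = √(6.3² + 3.2²) ≈ 7.0 points.
- Control hospitals only: deaths = 180 × 0.18 ≈ 32; standard error = √(0.667 × 0.333/32.4) ≈ 8.3 points; no bias.
- Pooled, HR 0.5: deaths = 360 × (0.4 × 0.232 + 0.06) ≈ 55; standard error = √(0.607 × 0.393/55) ≈ 6.6 points; bias 6.0 points; root mean squared error ≈ 8.9 points.

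So pooling has the smaller total error at HR 0.7, and control-only has the smaller at HR 0.5.

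**The case against.** - **Pooling is inferred.** The article never says that the conditions are combined, and data collection in every hospital is compatible with a stratified analysis specified elsewhere. That stands as a caution. But the article sets out both analysis steps and the elimination rule, and it compares the study groups explicitly for the intervention study. As written, the default for the indicator study is a pooled estimate.
- **The care may not change the events.** The shift is zero if it does not, and reverses if it raises event rates. The protocol itself says that no research data exist on a multidisciplinary approach in COPD for healthcare use or quality of life. A reader might infer that the estimates are certainly biased; the document supports only a conditional statement, on the trial's own hypothesis.
- **The extent is limited.** A reader might infer that about half the sample is affected, because half of the hospitals are. It is not: indicator-negative patients in intervention hospitals receive usual care, which leaves 16% to 24%.
- **The shift may be smaller than sampling error.** At HR 0.7 it is about 3 points of sensitivity against a standard error of about 6. That stands for one estimate, but the shift is systematic and proportionally larger for the odds ratio. For 8-week readmission nothing is quantified, and only a few contacts fall in that window.
- **Control hospitals alone are not clearly better.** This stands. They would supply about 32 deaths at 360 patients in all, or 270 × 0.18 ≈ 49 at 540, against 11 candidate indicators. Condition is also non-randomised, three hospitals against three.
- **The planned Cox model shows whether the care affected survival.** This helps interpretation but does not yield a usual-care estimate of discrimination.

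**Conclusion.** The concern holds in conditional form. The plan as written estimates discrimination without separating conditions, while a positive set triggers care in the intervention hospitals that the protocol expects to reduce the predicted events. If that expectation is right, pooled sensitivity, specificity and odds ratios understate discrimination under usual care. The shift originates in 16% to 24% of patients. Its size rests wholly on assumed mortality and effect: in the main example the odds ratio falls from 3.9 to 3.2–2.7 and sensitivity from 67% to 63–61%, with a small loss of specificity (66% to 65–64%).

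A reader might conclude that the control-hospital estimate must become the primary measure. The calculations do not settle that: which estimate has the smaller total error depends on an effect size that the document does not give. What they support is showing the results by condition and naming what the pooled figure represents.

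**What to change.** In Study parameter(s) indicator study, prespecify that:

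1. sensitivity and specificity are presented separately for control hospitals (the usual-care estimate) and intervention hospitals, alongside the pooled figure;
2. the logistic models include study condition;
3. one interaction, between condition and meeting two or more criteria, is examined. Condition as a main effect alone would not capture an effect confined to positive patients. A single interaction avoids one term per indicator, which the expected number of deaths could not support;
4. the pooled figure is interpreted as discrimination under mixed care.

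The data are already collected in both conditions, so only analysis wording changes. Settling it before outcomes are known avoids a later choice between estimates. The cost is precision: each by-condition estimate uses about half the patients, so its interval is about √2 ≈ 1.4 times wider. Because condition was not randomised, a difference between conditions may also reflect differences between hospitals, and the report should say so.

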#### Objectives indicator study

1. The primary objective is to assess the discriminating power of a set of indicators that indicates the start of proactive palliative care for patients with COPD.

2. The secondary objective is to examine to what extend individual indicators (or clusters) indicative are for the need of proactive palliative care.

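### Step 2 of the indicator study selects indicators at p < 0.10 and estimates them in the same patients, so retained odds ratios and any discrimination reported for the final model will be too favourable

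*Protocol article*

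**What the plan says.** The protocol article, under Statistical analysis, Study parameter(s) indicator study, states: "The analytical plan consists of two steps". The first step gives the sensitivity and specificity of the fixed rule that a patient meets at least two criteria. The second step is to "explore the discriminating power of individual indicators (or clusters) in predicting death within one year or unexpected admission to hospital".

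The method for the second step is written out. "Univariable and multivariable logistic regression will be performed to examine which variables or cluster of variables are associated with death within one year", and the same is done for unexpected admission. Then: "Variables will be eliminated one by one from the model based on likelihood ratio tests". And: "Variables are eligible for inclusion into the final model if they are significantly associated with death within one year" (or with unexpected admission), "with a p-value of < 0.10".

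This step serves the secondary objective of the indicator study, which is "to examine to what extend individual indicators (or clusters) indicative are for the need of proactive palliative care". It also serves secondary outcomes f, g and h, on the contribution of individual indicators. Table 1 lists eleven indicators, one of which (severe comorbidity) has five sub-items.

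**The concern.** The outcome data that decide which indicators stay also supply their odds ratios and any measure of how well the final model separates patients. An indicator survives partly because chance made it look strong in this sample. Three things follow:

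- indicators with no real association are kept;
- real ones that looked weak by chance are lost;
- the coefficients of the survivors are biased away from the null.

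Discrimination computed in the same patients is then higher than the same model would show in new patients.

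At stake is the answer to a named secondary objective. If the contribution of each indicator is read from the final model, the list errs in both directions and the strength of the listed indicators is overstated.

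**Working it through.** **Plan's own figure.** There is none to reproduce. The sample size section covers only the SGRQ comparison; no event count, precision or c-statistic is given for the indicator study.

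**Inputs from the article.** Six hospitals (Study design). An expected 60 to 90 patients each (Sample size calculation), so 6 × 60 = 360 to 6 × 90 = 540. Eleven indicators (Table 1), or 10 + 5 = 15 candidates if the comorbidity sub-items enter separately. One-by-one elimination by likelihood ratio test at p < 0.10.

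**Assumed, because the article gives no figure.** One-year mortality, indicator prevalences (15 to 50%), the correlation between indicators, and the number and strength of the true predictors.

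**Step 1: information available.** With mortality of 10 to 30%, deaths number 360 × 0.10 = 36 to 540 × 0.30 = 162. Per indicator that is 36/11 = 3.3 to 162/11 = 14.7, or 36/15 = 2.4 to 162/15 = 10.8 with fifteen candidates. Outcome h (death from pulmonary insufficiency) can have no more events than all-cause death.

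**Step 2: chance retention if nothing is predictive.** For eleven independent null indicators tested at 0.10, P(at least one kept) = 1 − 0.9^11 = 68.6%, and 11 × 0.10 = 1.1 are expected to be kept. Simulating the elimination itself, with weakly correlated indicators, gave 70 to 71%. The AUC was then 0.55 to 0.57 in the same patients against 0.50 in new ones.

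**Step 3: four of eleven indicators truly predictive, OR 1.8.** There were 400 runs per setting, with the selected model tested in 50,000 new patients. Optimism is taken before rounding. The mean OR is geometric, over true indicators that were kept.

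| N | Mortality | AUC, same patients | AUC, new patients | Optimism | At least one null kept | Mean OR if kept | True indicator dropped |
|---|---|---|---|---|---|---|---|
| 360 | 15% | 0.691 | 0.628 | 0.063 | 55% | 2.28 | 36% |
| 360 | 25% | 0.681 | 0.633 | 0.048 | 52% | 2.05 | 25% |
| 540 | 15% | 0.686 | 0.641 | 0.044 | 52% | 2.05 | 22% |
| 540 | 25% | 0.680 | 0.649 | 0.030 | 52% | 1.92 | 14% |

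The apparent gain over 0.50 is 0.191 in the first row, of which 0.063/0.191 = 33% is optimism. In the last row it is 0.030/0.180 = 17%.

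**Step 4: weaker predictors, four of eleven at OR 1.7.** There were 150 runs per setting.

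| N | Mortality | AUC, same patients | AUC, new patients | Optimism |
|---|---|---|---|---|
| 360 | 15% | 0.660 | 0.583 | 0.077 |
| 360 | 30% | 0.648 | 0.602 | 0.046 |
| 540 | 15% | 0.656 | 0.600 | 0.056 |
| 540 | 30% | 0.651 | 0.616 | 0.035 |

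The calibration slope in new patients was 0.52 to 0.79, where 1 means no overfitting. At least one null indicator was kept in 47 to 58% of runs.

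**Step 5: more true predictors.** With eight of eleven truly predictive, retention of at least one null indicator falls to 20 to 41%, but the optimism in AUC persists.

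**The case against.** The strongest reply is that the real complaint is the missing validation, and a condensed article may leave bootstrapping to a full protocol or analysis plan that is not shown. That is right as far as it goes: a reader might infer that no internal validation is planned, and the article's silence does not establish this. But the selection rule, its threshold and its purpose are all stated, and they produce the bias unless something is added.

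Three further objections stand and limit the point.

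- **Clinical use.** A reader might infer that a shortened list will be recommended to clinicians. No section says so. The second step is described as exploring, and the rule for use is fixed in advance as two or more of eleven criteria.
- **The primary question.** A reader might infer that the sensitivity and specificity of that rule are inflated too. They are not inflated by this procedure, because nothing in the rule is chosen from these data.
- **The metric.** The article names no AUC, c-statistic or calibration measure for the final model; it speaks only of discriminating power. The AUC figures therefore apply only if such a measure is reported.

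It is also fair to say that a threshold of 0.10 is lenient, so fewer real predictors are lost than at 0.05, and that indicators drawn from the literature may include few true nulls. Step 5 of the working shows that this reduces false retention but does not remove the optimism. The wording leaves open whether p < 0.10 is a univariable screen or a retention level; either way it uses the same outcome data.

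**Conclusion.** The concern holds for the exploratory second step of the indicator study, and only there. Followed as written, it gives a final model with some indicators kept by chance, some real ones missing and inflated odds ratios. In the settings examined, a true OR of 1.8 appeared as 1.92 to 2.28 when retained. Any discrimination reported for that model would be too high by about 0.03 to 0.08 in AUC.

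The direction was the same in every setting. The size rests on assumed mortality of 15 to 30%, assumed prevalences and assumed effects, and applies to the death outcome; readmission was not simulated. The optimism is modest in absolute terms. It matters because the AUC in new patients is itself only about 0.58 to 0.65 in the settings with four true predictors.

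**What to change.** Keep the elimination, labelled as exploratory, and add the following to the analysis text:

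- Report the full eleven-indicator model beside the reduced one for each outcome. Base statements on the contribution of individual indicators (outcomes f to h) on the full model or on shrunken coefficients.
- Repeat the whole selection, including any univariable screen, in each bootstrap sample (for example 500), and give the selection frequency of every indicator.
- If discrimination of the final model is reported, give it optimism-corrected from the same bootstrap, with the calibration slope.
- State whether p < 0.10 is a screen for entry or a level for retention.

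The cost is wording and some programming; no new data or patients are needed. The downside is that the reported discrimination will be less favourable.
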